## **Participants**

### **Inclusion criteria**

1. Be in a high-risk group for atopic sensitization: at least one of the father, mother, brothers, or sisters of infants has atopic diseases (asthma, atopic dermatitis, FA, allergic rhinitis, hay fever)

2. Obtained written informed consent.

a. Participants who understand randomization into two groups: BF with or without

amino acid milk and BF with CMF.

b. Blood examinations at 5-6 months and 2 years of age are required.

3. Be available to visit the outpatient clinic at 1 month, 2 months, 3 months, 4 months, 5 months, 7~8 months, 9~10 months, 12 months, 14~15 months, 18 months, and 24 months of age.

## **Exclusion criteria**

1. Less than 36 weeks of gestational age at birth or birth weight less than 2000 g.
2. Having serious congenital anomalies.
3. Being a triplet or more: twins may participate.
4. Abnormal delivery such as asphyxia (Apgar score 6 or less at 5 minutes after birth)

## **Interventions**

### **1. BF±EF**

Mothers in this group are asked to maintain exclusive BF. However, if the amount of breast milk is not sufficient, then EF may be added until starting solid food. If the mother needs to supply EF more than 150 ml/day for 3 consecutive days in addition to BF because of a low amount of breast milk, EF is switched to CMF. Thus, the offspring allocated to BF±EF can avoid CMF for at least the first 3 days of life.

### **2. BF+CMF**

Mothers in this group are asked to maintain exclusive BF, but are also asked to simultaneously supply a small amount of CMF  $\geq 5$  ml/day from the first day of life until 1 month, and  $\geq 40$  ml/day after 1 month until weaning. When infants are born after 18:00, CMF may be added on the 2nd day.

Both CMF (Hohoemi®) and EF (Meiji Elemental formula®) are purchased from Meiji Holdings Co. Ltd. (Chuo-ku, Tokyo, Japan).

### **EF (Meiji Elemental formula®)**

For infants with FA, total proteins are replaced with refined amino acids. However, other fats, carbohydrates, vitamins, and minerals are basically the same as in CMF. Energy is

66 kcal/100 ml (17%) and 391 kcal/100 g powder.

## **Outcome Measures**

### **Primary outcome**

#### **1. Atopic sensitization:**

The primary outcome was atopic sensitization to cow's milk protein, i.e., serum levels of cow's milk-specific IgE (CM-IgE)  $\geq 0.35$  UA/ml at 24 months of age. Serum levels of CM-IgE at 5 and 24 months of age as a continuous variable were used as reference values for primary outcome. Other atopic sensitization to egg white and wheat  $\geq 0.35$  UA/ml at 24 months of age were also evaluated to be compared with cow's milk sensitization. Outsourced for measuring with ImmunoCAP Specific IgE® (Thermo Fisher Diagnostics K.K., Minato-ku, Tokyo, Japan) to SRL Inc. and compared as both continuous and dichotomous (CM-IgE:  $\geq 0.35$  UA/ml) variable between BF±EF and BF+CMF group.

### **Secondary outcomes**

#### **1. Immediate type of FA**

Presenting with at least one organ symptom of skin (urticaria, angioedema, erythema, pruritus, periorbital edema, etc.), respiratory (dry staccato cough,

hoarseness, wheezing, etc.), gastrointestinal (nausea, vomiting, colicky abdominal pain, etc.), or circulatory (tachycardia, hypotension, loss of consciousness, etc.) problems triggered by the food ingestion that appeared within a few hours, in combination with blood examination measuring serum levels of the suspected food-specific IgE:  $\geq 0.35$  UA/ml by means of a fluorescence enzyme immunoassay.

In this trial, symptoms triggered by skin contact directly with food or indirectly with food-contaminated hands are not included.

The OFC test (Appendix 1) is performed around 1 year of age for infants who are sensitized to certain foods but for whom clinical reactivity after ingestion of the food allergen is unknown. Thus, immediate allergic reaction is a food-specific IgE:  $\geq 0.35$  UA/ml plus either a FA episode or positive OFC test. FA is re-evaluated regarding whether the infant could eat the causative food allergen without an allergic reaction at the 2-year-old birthday.

## **2. Anaphylactic type of FA**

When symptoms are derived from multiple (at least two of above) organs, e.g., urticaria and wheezing, the condition is defined as an anaphylactic reaction.

## **3. Desensitization of FA (= Sustained unresponsiveness or outgrow)**

If infants, who had been once diagnosed as immediate type of FA especially with cow's milk allergy, egg allergy, and wheat allergy, can eat the allergenic food (raw milk  $\geq 50$  ml, baked egg 30g, udon noodle 15g) without allergic signs by 2nd birthday, then they are defined as 'sustained unresponsiveness = outgrow' to the food allergen in this trial.

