**Secondary outcomes**

- I. Immediate type of food allergy (FA) including anaphylaxis
- II. Desensitization of FA (= sustained unresponsiveness, or outgrow)

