**Exploratory outcomes**

- I. Atopic dermatitis
- II. Asthmatic bronchitis

802 III. Sensitization to Japanese cedar pollen

803 IV. Allergic rhinitis

804  
805 **Study design**

806 Basic design: Parallel

807 Randomization: YES

808 Randomization unit: Individual

809 Blinding: Prospective, randomized, open, blinded-endpoint (PROBE) design

810 Control: Active

811 Stratification: NO

812 Dynamic allocation: NO

813 Institution consideration: NOT considered as an adjustment factor

814  
815 **Intervention**

816 No. of arms: 2

817 Purpose of intervention: Primary prevention of FA

818 Type of intervention: Food

819 1. **Intervention 1:** Breastfeeding (BF) with or without amino acid-based elemental formula  
820 (EF), called the BF±EF group (if the amount of breast milk is not sufficient, EF will be  
821 added), until starting solid food. When the mother needs to add EF of more than 150  
822 ml/day for 3 consecutive days to BF because of a low breast milk amount, EF is  
823 switched to cow's milk formula (CMF). Thus, the offspring allocated to BF±EF can avoid  
824 CMF for at least the first 3 days of life.

825 3. **Intervention 2:** BF plus CMF (≥5 ml/day from the first day of life to 1 month and ≥40  
826 ml/day after 1 month until weaning), called the BF+CMF group, until 5 months of age or  
827 starting solid food.

828  
829  
830 **Participants**

831 Age: Neonates at birth

832 Gender: Male and female

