## Hypotheses

1. Does avoiding exposure to CMF for the first 3 days of life prevent development of FA later?

This is the main hypothesis of this study and was explained in the 'Background'.

Many Japanese maternity wards encourage BF, but allow mothers or nurses to supplement BF with CMF, e.g., approximately 6 to 10 hours after birth or even earlier, based on maternal preferences, but not based on clinical evidence. However, more than 20 to 30 years ago, sugar water was given instead of CMF supplement at birth. Thus, we hypothesized that early exposure to CMF at birth may be associated with the recent increase in children with FA. Therefore, a randomized clinical trial (RCT) was conducted to assess whether the risk of CMF sensitization and FA is decreased by either avoiding or supplementing CMF at birth.

3. Vitamin D hypotheses

Refer to the review article by Dr. G. Lack.

The vitamin D hypothesis takes two forms: the vitamin D excess hypothesis argues that increases in vitamin D levels have led to increased allergies. The vitamin D deficiency hypothesis argues the opposite.

4. Dietary fat hypothesis

Refer to the review article by Dr. G. Lack.

The dietary fat hypothesis argues that reduction in consumption of animal fats and a corresponding increase in the use of margarine and vegetable oils have led to the increase in allergies. The argument is that there has been an increase in the consumption of  $\omega$ -6 polyunsaturated fatty acids, such as linoleic acid, and similarly that through reduced consumption of oily fish, there has been a reduction in  $\omega$ -3

polyunsaturated fatty acids, such as eicosapentaenoic acid.  $\omega$ -6 fatty acids lead to the production of prostaglandin E2 (PGE2), whereas  $\omega$ -3 fatty acids inhibit synthesis of PGE2. PGE2 reduces interferon- $\gamma$  production by T lymphocytes, thus resulting in increased IgE production by B lymphocytes. This has been proposed to explain the increase in the prevalence of asthma, eczema, and allergic rhinitis.

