### **II. Endpoint committee**

Among the following five members who do not know the allocation group and will not examine these participating infants at outpatient clinics, if  $\geq 3$  recognize the outcome as positive, the outcomes are finally determined to be positive.

1. [name]., Ph.D.
2. [name]., Ph. D.
3. [name]., Ph.D.

4. [name].

5. [name].

Department of Pediatrics

The Jikei University School of Medicine

Tokyo, Japan

What the committee is expected to determine.

These five members determine whether the infant has had an episode of FA or not.

0. No FA

1. Immediate allergic reaction

2. Anaphylaxis

For 1 (and 2) above, they determine the status at the second birthday by reviewing detailed episodes, results of the OFC test, and levels of food-specific IgE.

1. Sustained unresponsiveness

Cow's milk allergy, the infant can drink raw milk  $\geq 50$  ml

Egg allergy, the infant can eat baked egg  $\geq 30$ g,

Wheat allergy, the infant can eat udon noodle  $\geq 15$ g

2. Probable unresponsiveness, e.g., in the process of increasing dose of allergenic food, but not yet reach to predefined dose of unresponsiveness mentioned above.

3. Not yet unresponsive, when the infant eats, he or she still reacts to the allergenic food.

4. Not sure because the infant has not consumed the food allergen

The infants are still state of either 2, 3, or 4 above, they are considered not yet outgrow = remain food allergy.

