#### 5. Planned methods of analysis

Outcomes are analyzed by intention-to-treat analyses between the two comparative groups.

- a. Serum levels of cow's milk-specific IgE at 5 months and 24 months of age as a continuous variable are compared using Mann-Whitney test.
- b. Risk of cow's milk-specific IgE  $\geq 0.35$  UA/ml will be analyzed with a 2x2 table with the chi-square test and represented by the risk ratio (RR), and 95% confidence interval (95% CI).
- c. Secondary outcomes will be compared with RR, and 95% CI.
- d. Safety outcomes will be compared with RR, RD and 95% CI or Student's t test.
- e. Subgroup analysis will be done according to tertiles of 25(OH)D.
- f. All reported P values will be two-sided.
- g. Values with  $P < 0.05$  will be considered statistically significant.
- h. All data will be statistically analyzed using Stata 14.0 (StataCorp LP., College Station, TX, USA).

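### Desensitization of food allergy is compared between arms by RR with no stated denominator, although only infants who first developed food allergy can reach it; persistent food allergy over all randomised infants should carry the comparison

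*Supplement*

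**What the plan says.** All references are to the final version of the protocol and SAP in the Supplement.

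- **Status of the outcome.** The synopsis lists two secondary outcomes, and the second is "Desensitization of FA (= sustained unresponsiveness, or outgrow"). The full Secondary outcomes section has four headings: immediate-type FA, anaphylactic FA, desensitization, and each food allergy.
- **Who can reach it.** The definition under heading 3 begins "If infants, who had been once diagnosed as immediate type of FA". Under II. Endpoint committee, status at the second birthday is judged only for infants found to have had an immediate reaction or anaphylaxis. State 1 is sustained unresponsiveness. Of infants in states 2, 3 or 4 the plan says "they are considered not yet outgrow = remain food allergy".
- **How it is compared.** Planned methods of analysis, item c: "Secondary outcomes will be compared with RR, and 95% CI". The opening line of that section is general: "Outcomes are analyzed by intention-to-treat analyses between the two comparative" groups. No denominator is given for desensitization.
- **What the intervention is for.** The synopsis states "Purpose of intervention: Primary prevention of FA". The main hypothesis asks "Does avoiding exposure to CMF for the first 3 days of life prevent development of FA later".

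**The concern.** Whether an infant develops FA is decided after randomisation, and it is the event the trial tries to change. An outcome that exists only after that event cannot be compared between arms like the other secondary outcomes. There are two ways to form the RR.

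1. **Infants with FA as denominator.** This is the natural reading of the definition and of the committee's task. The two sets of FA infants are not randomised groups. If the arm that prevents FA mainly prevents cases that would have resolved, those left resolve less often and that arm looks worse. If it prevents mainly lasting cases, it looks better. Neither says anything about an effect on resolution.
2. **All randomised infants as denominator.** This follows from the general intention-to-treat sentence. The contrast is randomised, but an infant has to become allergic before it can count as a success, so the arm with more FA tends to score higher.

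The plan does not choose between the two, and they can give different answers from the same data. At stake is the reading of one secondary outcome: a lower or higher proportion outgrowing FA could be reported as harm or benefit when it reflects only how many infants, or which infants, became allergic.

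**Working it through.** **The plan's own figure.** The only calculation in the plan is the sample size for cow's milk sensitization: 10% vs 25%, two-sided alpha 0.05, power 90%.

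- Without continuity correction: n = [1.960·√(2·0.175·0.825) + 1.282·√(0.10·0.90 + 0.25·0.75)]² / 0.15² = 132.8, so 133 per arm.
- With it: n = (132.8/4)·[1 + √(1 + 4/(132.8·0.15))]² = 145.8, so 146 per arm, as stated.
- 292/0.97 = 301, against 300 stated.

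The figure reproduces. It concerns the primary outcome only; there is no calculation for FA or desensitization.

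**Inputs for the check.** 150 infants per arm (synopsis). The documents give no FA or resolution rates, so these are assumed. FA risk is set at 25% vs 10% (borrowed from the sensitization rates), 20% vs 10%, and 10% vs 5%. The effect is taken as purely preventive: one arm avoids some FA cases, and resolution in infants who still get FA is unchanged. An RR measuring an effect on resolution should therefore equal 1 throughout.

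**Formulas.** Let F₁ and F₀ be the FA cases in the preventing and the other arm, a the proportion of prevented cases that would have outgrown FA, and b that proportion in the remaining cases.

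- Outgrown, preventing arm: O₁ = F₁·b
- Outgrown, other arm: O₀ = F₁·b + (F₀ − F₁)·a
- RR among FA infants = (O₁/F₁)/(O₀/F₀)
- RR of outgrowing, all randomised = O₁/O₀, which equals (F₁/F₀) × (RR among FA infants)
- RR of persistent FA, all randomised = (F₁ − O₁)/(F₀ − O₀)

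**Worked row.** For 25% vs 10%: F₀ = 37.5, F₁ = 15. With a = 0.8 and b = 0.2: O₁ = 3 and O₀ = 3 + 22.5·0.8 = 21. Among FA infants: (3/15)/(21/37.5) = 0.20/0.56 = 0.36. Outgrowing over all: 3/21 = 0.14. Persistent FA over all: 12/16.5 = 0.73.

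| FA risk | a / b | RR among FA infants | RR outgrown, all | RR persistent FA, all |
|---|---|---|---|---|
| 25% vs 10% | 0.8 / 0.2 | 0.36 | 0.14 | 0.73 |
| 25% vs 10% | 0.7 / 0.3 | 0.56 | 0.22 | 0.61 |
| 25% vs 10% | 0.5 / 0.5 | 1.00 | 0.40 | 0.40 |
| 25% vs 10% | 0.3 / 0.7 | 1.52 | 0.61 | 0.22 |
| 20% vs 10% | 0.8 / 0.2 | 0.40 | 0.20 | 0.80 |
| 20% vs 10% | 0.7 / 0.3 | 0.60 | 0.30 | 0.70 |
| 20% vs 10% | 0.5 / 0.5 | 1.00 | 0.50 | 0.50 |
| 20% vs 10% | 0.3 / 0.7 | 1.40 | 0.70 | 0.30 |

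FA risks of 10% vs 5% give the same ratios as 20% vs 10%.

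**Two small examples with intervals** (log-Wald, assumed counts, 150 per arm).

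- FA in 30 vs 15 infants, half outgrown in each arm. Over all infants: (15/150)/(7.5/150) = 2.0 for the arm with twice the FA. Among FA infants: RR 1.0, SE = √(1/15 − 1/30 + 1/7.5 − 1/15) = √0.1, 95% CI 0.54 to 1.86.
- One arm has 10 mild cases (90% outgrown) and 10 severe (10% outgrown): 10/20 outgrown. The other prevents 8 of the mild cases: 2·0.9 + 10·0.1 = 2.8 of 12 outgrown. RR = 0.233/0.5 = 0.47, SE = √(1/2.8 − 1/12 + 1/10 − 1/20) = 0.569, 95% CI 0.15 to 1.42. FA falls from 20 to 12 and persistent FA from 10 to 9.2, while the RR among FA infants points against the preventing arm.

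**The case against.** Several counter-arguments have weight.

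- **The plan names no denominator.** A reader might infer that it commits to an RR among FA infants. The definition and the committee's task suggest this, but it is not written. The documented fault is the unstated denominator of a conditional outcome, and the rest follows reading by reading.
- **The RR of 2.0 depends on the less natural reading.** Among FA infants the same example gives 1.0, with no distortion.
- **The all-infants RR is causal.** A reader might infer that neither RR answers a causal question. That goes too far: over all randomised infants it is a valid randomised contrast for FA that arose and then resolved. The difficulty is only that a higher value is not a benefit.
- **The bias among FA infants needs a difference in prognosis** between prevented and remaining cases. Without one the RR is 1, and the documents give no rates from which to judge. Even the strongly contrasted mild/severe example has an interval that includes 1.
- **Part of the protection is already there.** FA itself is the first secondary outcome, and reporting it alongside would reveal an arm with more FA. FA is also re-evaluated at the second birthday, and the committee classes states 2 to 4 as remaining allergic.

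These points limit the size of the concern but do not remove it. No section makes persistent FA over all randomised infants a between-arm outcome, and nothing says how the desensitization RR is to be formed or read.

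**Conclusion.** The point stands as a should-fix. Desensitization depends on a post-randomisation status that the intervention targets, and its RR has no stated denominator. Under the assumed rates and a purely preventive effect, the RR among FA infants runs from 0.36 to 1.52 although resolution is unaffected. The RR of outgrowing over all infants runs from 0.14 to 0.70, against the preventing arm every time. Persistent FA over all infants gives 0.22 to 0.80, in favour of the preventing arm. The direction of the last two ranges follows from assuming pure prevention; the sizes are illustrations, not forecasts.

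A reader might infer that a main result of the trial is likely to point the wrong way. The documents do not support that. The sample size rests on cow's milk-specific IgE, which is unaffected; desensitization is one of four headings in the full secondary section; no secondary outcome is powered; and a reversal is shown to be possible, not probable.

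**What to change.** 1. Add FA persisting at the second birthday (committee states 2, 3 or 4) as a secondary outcome over all randomised infants, compared with RR, RD and 95% CI. Infants who never had FA count as not having it.
2. State the denominator for desensitization. Report it among FA infants as a descriptive, non-randomised result, with the number of FA infants per arm beside it.
3. Optionally, add a sensitivity analysis that does not count state 4 as persistent. In that state the infant has not eaten the food, so tolerance is unknown, and families know their allocation. The documents give no evidence that avoidance differs by arm.

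The outcome need not be removed. The committee already records the required states, so no new data are needed. The cost is a few lines of protocol and SAP text, one more reported outcome, and a smaller inferential role for desensitization.

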## **4. Each food allergy**

- a. Cow's milk allergy was defined allergic reaction by OFC-test or cow's milk intake with or without heated or processed with cow's milk-specific IgE are positive ( $\geq 0.35$  UA/ml).

b. Egg allergy was defined allergic reaction by OFC-test or egg intake with or without heated or processed with egg white-specific IgE are positive ( $\geq 0.35$  UA/ml).

c. Wheat allergy was defined allergic reaction by OFC-test or wheat intake with or without heated or processed with wheat-specific IgE are positive ( $\geq 0.35$  UA/ml).

d. Other food allergy was defined allergic reaction by OFC-test or a certain food intake with or without heated or processed with the food-specific IgE are positive ( $\geq 0.35$  UA/ml).

**Exploratory outcomes:** which are planned to report in another opportunity.

#### **1. Atopic dermatitis**

Check the SCORAD index at the 1- and 3-month check-ups.

#### **2. Asthmatic bronchitis**

A stringent index that includes frequent wheezing during the first 3 years of life and either one major risk factor (parental history of asthma or eczema) or two of three minor risk factors (eosinophilia, wheezing without colds, and allergic rhinitis).

Major Criteria

1. Parental asthma†

2. Eczema diagnosed by a medical doctor‡

3. Sensitization with elevated mite- or house dust-specific IgE  $\geq 0.10$  UA/ml

Minor Criteria

1. Allergic rhinitis diagnosed by a medical doctor§

2. Wheezing apart from colds

3. Eosinophilia ( $\geq 4\%$ )

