**Study period**

Accrual, if the number of randomized participants reaches >300, then entry is stopped.

The trial ends when the last participant is followed up after the 2-year-old birthday.

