## **Follow-up**

Participating parent(s) are interviewed, and their children are examined from 1 to 24 months of age at the outpatient clinic of Jikei University Hospital. All infants undergo blood examinations to measure serum levels of total IgE and antigen-specific IgE at 5 and 24 months of age. Unscheduled visits and blood examinations are performed at the clinic when a participating infant has atopic symptoms, particularly when FA is suspected.

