## Study design

Randomized, controlled, parallel two-group trial at a single institution

Pregnant women during the third trimester are randomly assigned to either BF with or without amino acid-based EF, called the BF $\pm$ EF group, or BF plus CMF ( $\geq$ 5 ml/day from the first day of life to 1 month and  $\geq$ 40 ml/day after 1 month until weaning), called the BF+CMF group, in a 1:1 ratio. Infants are followed until they are at least 2 years of age. Follow-up is extended 1 year if participating infants have FA. When the mother needs to add more than 150 ml/day EF for 3 consecutive days to BF because of a low amount of breast milk, EF is switched to CMF. Thus, the offspring allocated to BF $\pm$ EF can avoid CMF for at least the first 3 days of life.

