### 3. Study period

We assume that 100 pregnant women per year will participate in this trial. Therefore, the accrual period will be 3 years. The last infant is followed up 2 years later. Thus, a total of 5 years is predicted to be needed to accomplish this trial.

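### The exploratory asthmatic bronchitis index spans three years, but planned follow-up reaches a third year only in infants with food allergy

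*Supplement*

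**What the plan says.** All references are to the final protocol and SAP.

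- **Outcome window.** Exploratory outcomes, 2. Asthmatic bronchitis, uses "A stringent index that includes frequent wheezing during the first 3 years of life", combined with major or minor risk criteria.
- **Follow-up by FA status.** Study design states "Infants are followed until they are at least 2 years of age", and then "Follow-up is extended 1 year if participating infants have FA".
- **Visits.** The synopsis section Follow-up says "their children are examined from 1 to 24 months of age at the outpatient clinic of Jikei University Hospital". The visit lists in the inclusion criteria and in Flow of participants, section 3, also end at 24 months.
- **End of trial.** The synopsis section Study period says "The trial ends when the last participant is followed up after the 2-year-old birthday". Statistical analysis, 3. Study period, adds "The last infant is followed up 2 years later".
- **Analysis.** Section 5, Planned methods of analysis, calls for intention to treat. It sets no common cut-off age for this outcome and does not say how unequal follow-up is handled.
- **Status.** The exploratory outcomes are ones "which are planned to report in another opportunity".

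**The concern.** The window of the index and the planned follow-up do not match. For an infant without FA, no visit, questionnaire or other contact is planned in the third year, so a third of the window goes unseen. An infant with FA may be seen for all of it.

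FA arises after randomisation, and the main hypothesis is that the feeding intervention changes it. If the intervention works, the arms will differ in how many infants receive a third year. If wheeze from that year is then counted, part of any difference in asthmatic bronchitis reflects length of observation. Analysis by intention to treat does not remove this, because the problem lies in ascertainment and not in who is analysed. A comparison of asthmatic bronchitis by FA status would be affected more directly. Exploratory Aim 1 looks at FA and other atopic diseases side by side, so such a comparison is not far-fetched.

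**Working it through.** **The plan's own figure.** The plan gives no calculation for this outcome. Its only computed figure is the sample size for the primary outcome. That reproduces: 10% versus 25%, two-sided 5%, 90% power gives 146 per arm with continuity correction (133 without), 292 in all. Nothing below depends on it.

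**Coverage of the window.**
- Without FA: 24 / 36 = 67% of the window.
- With FA: up to 36 / 36 = 100%.
- The documents give no FA rate. If FA occurs in 5% to 25% of infants, then 300 × 0.95 = 285 down to 300 × 0.75 = 225 infants have no planned third year.

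**Late-enrolled infants with FA.** The plan foresees 3 years of accrual and 2 more years for the last infant, so closure at about month 60. An infant born in month *t* of accrual turns three in month *t* + 36, which falls after month 60 when *t* > 24. If the closing date is applied as stated, infants with FA born in the last of the three accrual years would not complete the extra year.

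**Possible distortion between arms if extension data are used.** Assume no true effect on wheeze, the same wheeze risk with and without FA, and a completed third year for every infant with FA. Let *f* be the FA proportion in an arm, and r24 and r36 the cumulative risks of meeting the index by 24 and 36 months. Then

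recorded risk = (1 − *f*) × r24 + *f* × r36.

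All rates are assumptions. The pair 10% and 25% is the plan's assumption for cow's milk sensitization, borrowed here for FA.

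| FA in the arms | r24 | r36 | Recorded risks | Risk ratio | Difference per 150 |
|---|---|---|---|---|---|
| 10% / 25% | 10% | 15% | 10.50% / 11.25% | 1.07 | 1.1 children |
| 10% / 25% | 10% | 20% | 11.00% / 12.50% | 1.14 | 2.3 children |
| 5% / 15% | 10% | 15% | 10.25% / 10.75% | 1.05 | 0.8 children |
| 5% / 15% | 10% | 20% | 10.50% / 11.50% | 1.10 | 1.5 children |

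First row in full: 0.90 × 10% + 0.10 × 15% = 10.5%; 0.75 × 10% + 0.25 × 15% = 11.25%; 11.25 / 10.5 = 1.07; 150 × 0.75% = 1.1.

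The ratio depends only on *f* and on the share *s* of three-year cases that first qualify in year 3. The table has *s* = 1/3 and 1/2. With *s* = 10% the ratio falls to 0.915 / 0.905 = 1.01 (FA 5% / 15%) and 0.925 / 0.910 = 1.02 (FA 10% / 25%).

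**Comparison by FA status.** Under the same assumptions the apparent risk ratio, FA versus no FA, is 1 / (1 − *s*): 1.11, 1.50 and 2.00 for *s* = 10%, 1/3 and 1/2.

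**The case against.** The strongest reply is that the plan never says that wheeze is collected in the third year, or that such data enter a comparison of the arms. Every visit list stops at 24 months, and no year-3 visit is set out even for infants with FA. On that reading all infants are assessed to 24 months, the three-year phrase merely comes with the cited index, and the defect is an unclear window. This stands in part: bias is a possibility that the plan leaves open, not one that it builds in. The mismatch between the outcome definition and follow-up remains on either reading, and no section resolves it.

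Three stronger inferences are tempting and do not hold:

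- **That the outcome is unobservable in infants without FA.** An infant who already meets the index by 24 months can be counted. What is lost is onset in year 3 and a confirmed negative.
- **That the extra year distorts the food allergy outcomes.** The definition "Other food allergy was defined allergic reaction by OFC-test or a certain food intake" carries no age limit, and neither does the anaphylaxis definition. But FA must be present before the extension starts, so the extra year cannot create a first case. The endpoint committee determines status at the second birthday, and immediate-type FA is re-evaluated then. At most, a further food or a later anaphylactic reaction could be added in an infant already counted as having FA.
- **That it distorts allergic rhinitis.** That outcome also needs mite-specific IgE, and scheduled sampling ends at 24 months.

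It is also fair to say that the outcome is exploratory, is to be reported separately, and that the illustrated distortion is about one to two children per arm.

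**Conclusion.** The point holds in limited form. The three-year window of the asthmatic bronchitis index is covered by planned follow-up only in infants with FA, and perhaps not fully in those enrolled late. If extension-year data are used, ascertainment depends on an outcome that the intervention targets. With no true effect, the spurious risk ratio (arm with more FA over arm with less) is about 1.05 to 1.14 under the tabulated rates, and nearer 1 if few cases first qualify in year 3. These figures rest wholly on assumed FA and wheeze rates and on completed third years. They show the possible size and are not an estimate. The primary outcome, fixed at 24 months, the sample size and overall immediate-type FA are unaffected. This is a cheap correction to an exploratory outcome and no threat to the trial's main conclusions.

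**What to change.** Make two changes of wording:

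1. In Exploratory outcomes, 2. Asthmatic bronchitis, define the wheezing window as birth to the 24-month visit for all infants.
2. In Statistical analysis, section 5, state that between-arm comparisons of this outcome use data up to the 24-month visit only, and that extension-year data are listed separately.

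Both rely on data already planned, so no visit is added. The cost is that the result is a 24-month wheeze index, no longer the cited three-year one, and should be labelled as such. Keeping the three-year index would instead require wheeze data to 36 months in every infant and a later end of trial, which is more than an exploratory outcome seems to warrant.
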